# Effectiveness and cost-effectiveness of embedded simulation in occupational therapy clinical practice education: study protocol for a randomised controlled trial

**DOI:** 10.1186/s13063-017-2087-0

**Published:** 2017-07-21

**Keywords:** Simulation, Occupational therapy, Clinical placement, Efficiency, Cost, Clinical reasoning, Trial, Evaluation, Education, Simulated clinical placement

## Abstract

**Background:**

Clinical placements are a critical component of the training for health professionals such as occupational therapists. However, with growing student enrolments in professional education courses and workload pressures on practitioners, it is increasingly difficult to find sufficient, suitable placements that satisfy program accreditation requirements. The professional accrediting body for occupational therapy in Australia allows up to 200 of the mandatory 1000 clinical placement hours to be completed via simulation activities, but evidence of effectiveness and efficiency for student learning outcomes is lacking. Increasingly placement providers charge a fee to host students, leading educators to consider whether providing an internal program might be a feasible alternative for a portion of placement hours. Economic analysis of the incremental costs and benefits of providing a traditional versus simulated placement is required to inform decision-making.

**Methods/design:**

This study is a pragmatic, non-inferiority, single-blind, multicentre, two-group randomised controlled trial (RCT) with an embedded economic analysis. The RCT will compare a block of 40 hours of simulated placement (intervention) with a 40-hour block of traditional placement (comparator), with a focus on student learning outcomes and delivery costs. Six universities will instigate the educational intervention within their respective occupational therapy courses, randomly assigning their cohort of students (1:1 allocation) to the simulated or traditional clinical placements. The primary outcome is achievement of professional behaviours (e.g. communication, clinical reasoning) as assessed by a post-placement written examination. Secondary outcomes include proportions passing the placement assessed using the Student Practice Evaluation Form-Revised, changes in student confidence pre-/post-placement, student and educator evaluation of the placement experience and cost-effectiveness of simulated versus traditional clinical placements. Comprehensive cost data will be collected for both the simulated and traditional placement programs at each site for economic evaluation.

**Discussion:**

Use of simulation in health-related fields like occupational therapy is common, but these activities usually relate to brief opportunities for isolated skill development. The simulated clinical placement evaluated in this trial is less common because it encapsulates a 5-day block of integrated activities, designed and delivered in a manner intended to emulate best-practice placement experiences. The planned study is rare due to inclusion of an economic analysis that aims to provide valuable information about the relationship between costs and outcomes across participating sites.

**Trial registration:**

Australian New Zealand Clinical Trials Registry, ACTRN12616001339448. Registered 26 September 2016.

**Electronic supplementary material:**

The online version of this article (doi:10.1186/s13063-017-2087-0) contains supplementary material, which is available to authorized users.

## Background

Clinical placements are integral to occupational therapy professional education. Theoretical knowledge derived from formal education needs to be supported by exposure to the practice environment for learning to be maximised [1–3]. Through immersion in workplace learning, clinical placements provide students with opportunities to synthesise theoretical and tacit knowledge to develop professional competencies [4, 5]. Fundamental elements of placements for any professional academic program provide students with opportunities to apply theoretical knowledge and practical skills developed during their course as well as engage in real-world practice and decision-making and in the role they are learning to become [6–9].

Varied terms have been used to describe clinical placements in the literature. For example, the World Federation of Occupational Therapists [10] uses the terms *fieldwork education* or *practice education* to refer to the professional practice placement component of educating student occupational therapists. Other terms include *clinical education* and *preceptorship*. In this paper the term *clinical placement* will be used in two ways as follows:
*Traditional clinical placement (TCP)* refers to the clinical placement experience that occupational therapy students undertake for their clinical education within a professional setting that provides services to the community. Such settings include hospitals, schools, private practices and various other for-profit and not-for-profit organisations.
*Simulated clinical placement (SCP)* refers to a collection of planned and integrated activities that aim to emulate a traditional clinical placement, in which the environment, people, materials, activities and processes of work are simulated to create a facsimile of occupational therapy practice.

Occupational therapy programs must adhere to the minimum standards for clinical placements specified by the World Federation of Occupational Therapists [10] and the Occupational Therapy Council (Australia & New Zealand) Ltd (OTC) for accreditation. Students must complete a minimum of 1000 hours of clinical placement during their degree [11]. However, universities find it increasingly difficult to source a sufficient number of quality clinical placements to provide all students with the opportunity to practise and demonstrate key clinical skills and professional competencies across a range of practice areas [12, 13]. This situation arises from a number of pressures associated with changes in work practices and organisational structures in healthcare, as well as programs on offer and the students who enrol in them. Specific examples of these pressures include the following: a shift of healthcare services from institutions to community settings; increased part-time work for supervisors, allowing less time for student supervision; more emphasis on risk management in patient care; and growing numbers of university occupational therapy training programs and more students enrolling in them [13–15].

Innovative teaching and learning strategies are required to ensure students are provided with quality clinical placements throughout their professional education. To meet these learning needs, simulation-based learning has been utilised as an educational strategy in medicine [16], nursing [17–19] and allied health [20]. A project conducted in 2010 by a team from the University of Queensland (UQ) on behalf of Health Workforce Australia examined the use of simulation in occupational therapy curricula [21]. The project reviewed all Australian occupational therapy programs and identified only three that utilised simulation-based learning to replace any part of a clinical placement. These three programs counted between 5 and 15 hours of simulation-based learning towards the 1000 hours of required placement. Rodger et al. [9] identified several main barriers to implementing a sustainable simulation-based learning program. These barriers included a lack of resources such as simulated environments, limited access to standardised (simulated) patients and issues of sustainability related to recurrent funding and training needs.

The potential for simulation-based learning activities to replace some clinical placement hours to increase placement capacity and improve readiness of students to commence clinical placements was identified [21]. A key outcome of the project was the development of a consensus statement regarding the extent and quality criteria for simulation-based learning. This consensus stated that up to 20% of the required 1000 hours of clinical placement could be delivered via simulation activities, provided the following design and delivery conditions were met:High level of authenticity for occupational therapy practiceHigh level of complexity requiring student engagement and interactionImmediacy to interaction with a real client and to occupational therapy clinical placementsAssessed with respect to meeting occupational therapy clinical placement objectivesNo one simulation modality to be used as a ‘stand-alone’ alternative to clinical training time ([21], p. 6)

Following public consultation, the OTC [11] finalised new accreditation standards for Australian occupational therapy programs of study, and these were approved by the Occupational Therapy Board of Australia in 2013. The approved standards stipulated that up to 20% of a minimum of 1000 hours of clinical placement (200 hours) may include well-designed simulation-based learning activities. Published explanatory guidelines elaborated the standard requirements for simulation when used for clinical placement. The guidelines identified the potential for simulation activities to be used to ensure students are adequately prepared to commence clinical placement, to ensure students achieve threshold competencies and safe practice and to enhance learning and reasoning in follow-up to clinical placement. Additionally, the guidelines stated that simulation-based learning activities that contribute to clinical placement hours must meet the five criteria identified previously [21]. Importantly, the OTC [11] guidelines stipulated that student interaction with a real client may be with a standardised (simulated) patient. This provides the opportunity for simulation to be used as a full substitute for up to 200 of the required 1000 clinical placement hours, rather than only to augment clinical placement experiences.

Few studies have evaluated the effectiveness of using simulation to substitute TCPs in allied health. In one study [22], randomised controlled trials (RCTs) were used to investigate whether simulated learning environments (SLEs) for physiotherapy can, in part, substitute for a TCP experience. A simulation program was developed to replicate clinical placement in musculoskeletal practice in an ambulatory care setting to replace 1 week of a 4-week clinical placement. Three hundred and seventy physiotherapy students from six universities in Australia participated in an RCT. It was concluded that students’ achievement of clinical competencies was equivalent between the SLE and TCP groups.

Two independent, parallel, single-blinded, multicentre RCTs were conducted [23] to compare physiotherapy students’ achievement of clinical competencies in SLEs against traditional cardiorespiratory clinical placement. Students participated in practice learning in a traditional ward setting or a simulated ward environment. Either a simulated patient or a high fidelity simulator was used in the simulated ward. A total of 349 physiotherapy students from seven universities participated in these trials. Student performance was comparable between the SLE groups and the TCP groups. Students were also satisfied with their simulation learning experience. Evidence from this study supported the notion that simulated clinical experiences can replace part of a clinical placement and achieve no worse outcomes. The work of Watson et al. [22], Blackstock et al. [23] and an unpublished simulation pilot program at Australian Catholic University in occupational therapy suggest that simulation-based learning can be an effective alternative to TCP in allied health professional education. However, further empirical evaluation is needed.

There is a body of literature describing the benefits of simulation for training and education, though rigorous evaluations are more sparse [24]. There is evidence to indicate benefit in using simulated clients/patients for fostering patient-centred skills for students in nursing [25] and psychiatry [26]; that simulation use can improve knowledge, skills and attitudes as part of a larger program for physical therapy students [24]; and that it is beneficial for specific medical interventions such as resuscitation [27]. A comprehensive systematic review and meta-analysis [28] found small but positive overall benefits for simulation for students in medicine, nursing, dentistry, emergency medicine and other medical fields, but those benefits were associated with a higher cost. However, a longitudinal study [29] found no skill-based benefit amongst nursing students who had undertaken the simulation curriculum, and a large longitudinal study involving nursing students [30] found no difference at the time of final assessment after replacing either 25% or 50% of traditional clinical hours with simulation versus a control group.

Applying the knowledge gained from prior research to occupational therapy programs needs to be considered in light of the technologies and techniques used in the healthcare simulation field, which are often specific to discipline practices and constantly evolving. Thus published research can date quickly or be difficult to generalise. There is also significant variation in what is meant by the term *simulation*. Learning activities can be defined as simulation when students watch video footage of procedures being demonstrated, or actors are hired to play the role of patient/client or when students engage with an interactive computer-based activity or medical device. Simulation is also the term used when a fully immersive virtual reality experience is provided. What outcome is studied in research also varies, increasing the complexity of interpreting and using the findings. Thus carefully conducted empirical studies, with clearly defined procedures, and systematic reviews of research are of the greatest value for informing educational practices. In addition, education providers need to make decisions about resources that are fiscally responsible. It is possible that simulation may be able to provide an effective learning environment for some student outcomes, but the cost of achieving this is not known.

The purpose of the current project is to compare the learning outcomes between those students who undertake an SCP and those students who undertake a TCP, and to assess the costs of developing and maintaining the SCP compared to sourcing and implementing TCPs. The study will focus on students in the earlier years of their occupational therapy degree programs and on determining whether students who experience an SCP achieve non-inferior outcomes compared to those who experience a TCP. Efficacy, cost-effectiveness and affordability results will inform universities considering these placement activities.

## Methods

### Design

The study is a pragmatic, non-inferiority, single-blind, multicentre, two-group RCT with an embedded economic analysis. Figures 1 and 2, respectively, display a flowchart and a Standard Protocol Items: Recommendations for Interventional Trials (SPIRIT) chart of assessment data for the study. A populated SPIRIT checklist is provided in Additional file 1.

**Fig. 1 Fig1:**
[figure not shown]
Flow diagram of the RCT of simulated clinical placement (*SCP*) versus traditional clinical placement (*TCP*) programs

**Fig. 2 Fig2:**
[figure not shown]
SPIRIT chart for stages of assessment in this RCT. A populated SPIRIT checklist is available in Additional file 1

### Aims and research questions

The study aims to explore the differences between a 40-hour block SCP experience and a 40-hour block TCP experience in terms of development of professional competencies and fieldwork confidence, and to determine the comparative delivery costs for the SCP and TCP programs as borne by the university.

The research questions are:Do students who undertake an SCP in the early years of an entry-level occupational therapy program achieve *non-inferior outcomes* in their development of professional practice skills compared with those who attend a TCP, as assessed by a post-placement written examination (primary outcome), Student Practice Evaluation Form-Revised (SPEF-R) evaluation [31, 32] and end-of-semester study unit score?Do students and supervisors report similar professional practice learning opportunities when students complete an SCP compared to those students who complete a TCP, assessed using a self-report survey, and similar frequencies of *not applicable* and *insufficient observation* items in the SPEF-R?Economic research questions: If non-inferiority is established, does SCP cost less than TCP from the perspective of (1) the health sector and (2) the universities as providers?If costs of SCP are not less than those of TCP, are there offsetting benefits which still make the SCP value for money?
Do students who experience an SCP in the early years of an entry-level occupational therapy program report self-confidence outcomes that are non-inferior to those who attend a TCP, as measured by the Student Confidence Questionnaire [33]?What are the perceptions of quality and adequacy of the TCP versus SCP experience of students and clinical educators?

### Location and timing

The multicentre trial will be coordinated from one university by a national research team. It will be delivered, and separately managed, at six universities by local implementation teams. One of those universities will implement the trial at three campuses; thus the trial will be implemented at eight different sites. The clinical placement experience will be integrated into a unit of study within occupational therapy courses at each university at a time during 2016 deemed most appropriate by each course convenor. Thus, while the placement block (SCP and TCP) occurs across a consistent and intensive 5-day period, the timing of delivery of that block is at the discretion of each course convenor to ensure best fit with each university’s individual curriculum and any other local considerations.

In some cases the trial placement program replaces existing placement hours within the course, and in others the course convenor may elect to add the intensive week to existing placement arrangements. Any modifications to curricula that are required to embed the placement experience into the units of study will be made by course convenors and subject to appropriate university approvals obtained prior to implementation. Due to the geographical distribution of sites across Australia and the different systems employed at each university, each site will have its own local implementation team that includes a site coordinator, various academic and clinical staff and a local research assistant. The economic appraisal is coordinated and conducted across all sites by one economic team.

### Participants

All students enrolled in the chosen units at each participating university are required to complete the placement program (TCP or SCP) as part of their studies and are eligible to participate. All of these students are also required to complete the various instruments used to collect data for the study, some of which form part of the assessment for their studies. Participation in the research (as opposed to participation in the placement program) involves students consenting for their data to be included in the trial. Data from students who do not consent to participate will be used for local assessment purposes where relevant, and destroyed where not relevant. Only data from consenting students will be submitted to the investigator team. Participation in the RCT study is voluntary. Students who are repeating the unit of study are ineligible to participate in the trial (but may still complete the unit of study and the placement program). There are no other exclusion criteria. Along with student participants, clinical supervisors and educators involved in the delivery of the placement program (TCP and SCP) are eligible to participate. Their participation is voluntary, and informed consent will be obtained.

#### Sample size

The SCP has been trialled at the managing university within a second-year level unit of study in an undergraduate occupational therapy bachelor degree. This provided a set of indicative student outcomes allowing for calculation of a sample size estimate. The primary outcome used for this calculation was the post-placement examination score (range 0–100%). Non-inferiority was defined as a mean score difference in exam scores between SCP and TCP groups of ≤7%. This value was based on the standard deviation of student examination scores obtained within the unit of study where the SCP was piloted in 2013.

Using standard power estimate criteria (to achieve a power of at least 0.8, alpha level 0.05), 120 students per group are required (total sample = 240). To account for clustering according to university site, where an average cluster size of 50–60 students is anticipated, and an estimated intraclass correlation coefficient (ICC) of 0.007, an additional 100 students will be required (*n* = 340). Finally, to allow for a 20% attrition rate (340/0.8), a total sample of 425 participants is required.

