#### Statistical analyses methods

All data will be entered into a purpose-designed REDCap (https://projectredcap.org/) database, cleaned and assessed for missing data. Summary statistics will be used to describe the sample. To evaluate whether students who attend an SCP achieve non-inferior outcomes to those who attend a TCP, differences in achievement on the post-placement examination score will be evaluated using analysis of covariance (ANCOVA). A mean difference of ≥7 points on the examination score between students will be considered an educationally meaningful difference. Covariates included in the analyses will include broad placement type (vocational rehabilitation, physical rehabilitation or mental health) and any demographic variables identified as important during baseline analyses. Secondary outcomes related to whether students who attend an SCP achieve non-inferior outcomes to those who attend a TCP will be assessed using odds ratios between groups in predicting overall pass/fail grades on the SPEF-R, evaluated using binary logistic regression. Independent variables included in the analyses as possible covariates will include gender, age, broad placement type and any demographic variables identified in baseline analyses as important. Differences between SCP and TCP groups in achievement of a pass/fail grade on each of the four completed sections of the SPEF-R will be assessed using chi-square tests. Scores between SCP and TCP groups for individual SPEF-R items (scored on a 5-point ordinal scale) will be compared using a Mann-Whitney *U* test. An overall difference >1 point on the 5-point scale between groups will be considered educationally important.

To evaluate whether students and clinical educators report similar professional practice learning opportunities during SCP compared to TCP, the differences in frequencies of *not applicable* and *insufficient observation* items checked in the total SPEF-R by (1) students and (2) clinical educators will be compared using an independent samples *t* test, using 95% confidence intervals of the estimated mean difference between groups to identify differences.

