The current trial includes design elements that will support dissemination and knowledge transfer across occupational therapy programs in Australia. Multisite trials that aim to exert high levels of control of the trial’s implementation would typically centrally train an SCP delivery team and data collection team and dispatch them to each university to implement the SCP program in parallel with that university’s TCP program. While this might provide evidence of the effect of a highly controlled intervention, the current study is pragmatic and will provide evidence of the effectiveness of a ‘real-world’ implementation because each university is responsible for implementing the RCT, in terms of delivering the program as well as collecting the data, at their own institution. Our protocols include provision of training via a training officer, the trial manager and one of the lead investigators visiting each site to prepare the local team to deliver the SCP, administer the RCT processes and collect the data. Detailed manuals and checklists have also been prepared and ongoing support put in place to assist each site. While a pragmatic approach entails some risk to the consistency of the implementation of the RCT, these risks are offset by both the practical advantages of having local teams implement the program and the increased rapidity of knowledge translation following trial completion through ongoing use of the materials and resources developed for the project — if the hypothesis that the two placement modes are equivalent is supported by the data. Local management also reflects how a placement program would be run at a university.

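### The primary non-inferiority criterion is stated only as a mean difference of 7 points, with no subtraction order and no confidence limit compared with the margin

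*Protocol article*

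**What the plan says.** The Sample size section defines the criterion: "Non-inferiority was defined as a mean score difference in exam scores between SCP and TCP groups of ≤7" per cent, on a 0–100% examination score. On where the 7 comes from it says: "This value was based on the standard deviation of student examination scores obtained within the unit of study where the SCP was piloted in 2013". The SD itself is not printed. The design criteria are "to achieve a power of at least 0.8, alpha level 0.05", without saying whether alpha is one- or two-sided, and they lead to "120 students per group are required (total sample = 240"). That total is raised to 340 for clustering by site and to 425 for attrition.

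Under Statistical analyses methods, "differences in achievement on the post-placement examination score will be evaluated using analysis of covariance (ANCOVA"). The next sentence reads: "A mean difference of ≥7 points on the examination score between students will be considered an educationally meaningful difference". The only confidence interval in that section belongs to another outcome, the counts of SPEF-R items marked not applicable or insufficiently observed: "using 95% confidence intervals of the estimated mean difference between groups to identify differences".

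The Background and the Aims and research questions section ask a one-directional question, whether SCP students do no worse than TCP students. The Economic evaluation section makes cost-minimisation conditional on non-inferiority having been established.

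**The concern.** A non-inferiority claim needs evidence that the true deficit is smaller than the margin. That means comparing a confidence limit, or an equivalent test, with a signed margin. The article has a margin and a model but does not join them.

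- A standard ANCOVA tests the group difference against zero. A non-significant result does not show non-inferiority, and an estimate inside 7 points does not either, because neither accounts for sampling error relative to the margin.
- Without a subtraction order, the literal criterion changes meaning. As SCP minus TCP of at most 7, any deficit passes. As an absolute difference, an SCP more than 7 points better fails.

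This is the primary decision, and it also determines whether a cost-minimisation analysis is used. Following the text as written gives no controlled rate of wrongly declaring non-inferiority.

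**Working it through.** **Inputs from the article.** Margin 7 points; power 0.8; alpha 0.05, sidedness not stated; 120 per group; site cluster size 50–60; ICC 0.007; 340 evaluable students; 20% attrition; 1:1 allocation. **Assumption:** the SD is not given, so it is back-solved from 120 per group with a true difference of zero.

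**1. The plan's own figures.** SD = 7 × √(120/2) / (z_alpha + 0.842), with 7 × √60 = 54.22.
- Two-sided 0.05 (one-sided 0.025): 54.22 / (1.960 + 0.842) = 19.35.
- One-sided 0.05: 54.22 / (1.645 + 0.842) = 21.8.

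So 120 per group cannot be verified, only shown to imply an SD of about 19.4 or 21.8. The later steps reproduce: 240 × (1 + 59 × 0.007) = 240 × 1.413 = 339.1, hence 340 (with cluster size 60; 322.3 with 50), and 340/0.8 = 425.

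**2. Standard error of the difference.**
- 340 counted as independent, SE = SD × √(2/170): 2.10 (SD 19.35) or 2.36 (SD 21.8).
- Design effect charged in full (340/1.413, about 240), SE = SD × √(2/120): 2.50 or 2.81.

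**3. Literal rule.** With true deficit D (TCP minus SCP), P(estimated deficit ≤7) = Φ((7 − D)/SE).
- D = 7: Φ(0) = 50%, whatever the SD or sample size.
- With 340 independent, D = 8: 34% (SE 2.36) or 32% (SE 2.10). D = 9: 20% or 17%.
- With effective n about 240, D = 9: 24% (SE 2.81) or 21% (SE 2.50).

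**4. Confidence-limit rule.** P(pass) = Φ((7 − D)/SE − z).
- D = 7: 2.5% with a two-sided 95% interval, 5% with a 90% interval.
- 95% interval and 340 independent: 0.7–0.9% at D = 8, about 0.2% at D = 9.

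**5. Which reading fits the stated power.** At zero true difference with 120 per group and SD 19.35, the literal rule passes with probability Φ(7/2.50) = 0.9975. The 95% confidence-limit rule passes with probability Φ(7/2.50 − 1.96) = 0.80, the stated power.

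**6. An example of the gap.** With SE 2.50, take an observed SCP deficit of 4 points. Against zero, z = 4/2.50 = 1.6, not significant. The estimate is within 7. Yet the lower 95% limit for SCP minus TCP is −4 − 1.96 × 2.50 = −8.9, beyond −7. To pass the 95% rule the observed deficit must be below 7 − 1.96 × 2.50 = 2.1 points.

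**7. Power at zero true difference, 95% rule.**
- 340 independent: Φ(7/2.36 − 1.96) = 84% to Φ(7/2.10 − 1.96) = 92%.
- Effective n about 240: Φ(7/2.81 − 1.96) = 70% to Φ(7/2.50 − 1.96) = 80%.

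**The case against.** The strongest defence is that the 7-point definition stands in the Sample size section, beside an alpha and a power, where the natural reading is a margin on the true difference. Step 5 supports this: a point-estimate rule would have had about 99.7% power, not 0.8. A reader might infer that the trial has adopted a rule on the observed difference. The article does not say observed, so that inference is not secure. The 50% figure is also a property of any point-estimate rule and says nothing specific about this trial. This part of the defence stands, and the 50% is therefore conditional on the literal reading.

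It can also be said that an article may leave the confidence limit to a fuller document. That would answer a mere omission. Here, however, the article states the criterion in a particular form and then, in the analysis section, offers only a zero-difference method and a second bare threshold.

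Three further inferences are tempting and not supported:
- That the direction of the hypothesis is unknown. The Background and the research questions make it clear; only the subtraction order is unwritten.
- That the two thresholds conflict materially because exactly 7 satisfies both. On a continuous score this is trivial, and the analysis section's threshold is labelled as educational meaning, not as the non-inferiority rule.
- That the trial tests equivalence, because the Discussion says "if the hypothesis that the two placement modes are equivalent is supported by the data". This is one loose clause against consistent non-inferiority wording elsewhere, and is editorial.

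**Conclusion.** The point holds in this form: the primary criterion appears only as a mean difference analysed by ANCOVA, with no subtraction order and no confidence limit set against the margin. On the literal reading (estimated TCP minus SCP), a true 7-point deficit passes 50% of the time, against 2.5% or 5% under a 95% or 90% interval. On the more natural reading of 7 as a margin on the true difference, the design is coherent, but the analysis section does not carry out the test that the design assumes. Either way the primary decision rule needs rewriting.

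The 50% needs no SD. The figures at 8 and 9 points and all the power figures rest on an SD of 19.4 or 21.8 back-solved from 120 per group. The power figures also depend on how site clustering is charged. The article inflates 240 to 340 for it, so it cannot be taken for granted that 340 behave as independent. Because allocation is within site, the full charge may be pessimistic.

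**What to change.** In both the Sample size and the Statistical analyses methods sections, state that SCP is non-inferior if the lower confidence limit for the adjusted mean difference in examination score (SCP minus TCP) lies above −7 percentage points. Keep the threshold of 7 points or more only as an aid to interpretation. Replacing the Discussion's equivalence wording is an optional tidy-up.

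Name the confidence level to match the alpha used for 120 per group:
- two-sided 95% if it was two-sided 0.05 or one-sided 0.025 (implied SD about 19.4);
- two-sided 90% if it was one-sided 0.05 (implied SD about 21.8).

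The 95% level is the conventional, stricter choice, but the article does not settle it. Printing the pilot SD would show which calculation was used.

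The cost is that non-inferiority is harder to claim. If 120 per group came from one-sided 0.05 and a 95% interval is adopted, power falls to about 70% with the design effect charged in full, below the stated 0.8; matching the level with a 90% interval keeps it at 80%. The change is one of wording and needs no new data. Because the Trial status section reports data collection complete at acceptance, the rule and its date should be recorded before the groups are compared, or the report should say that it was set afterwards.
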